## 7.2 Adverse Event Characteristics

- CTCAE term (AE description) and grade: The descriptions and grading scales found in the revised NCI Common Terminology Criteria for Adverse Events (CTCAE) version 4.0 will be utilized until March 31, 2018 for AE reporting. CTCAE version 5.0 will be utilized for AE reporting beginning April 1, 2018. All appropriate treatment areas should have access to a copy of the CTCAE version 5.0. A copy of the CTCAE version 5.0 can be downloaded from the CTEP web site [http://ctep.cancer.gov/protocolDevelopment/electronic\\_applications/ctc.htm](http://ctep.cancer.gov/protocolDevelopment/electronic_applications/ctc.htm)
- For expedited reporting purposes only:
  - AEs for the agent that are ***bold and italicized*** in the CAEPR (*i.e.*, those listed in the SPEER column, Section 7.1) should be reported through CTEP-AERS only if the grade is above the grade provided in the SPEER.
- **Attribution** of the AE:
  - Definite – The AE *is clearly related* to the study treatment.
  - Probable – The AE *is likely related* to the study treatment.
  - Possible – The AE *may be related* to the study treatment.
  - Unlikely – The AE *is doubtfully related* to the study treatment.
  - Unrelated – The AE *is clearly NOT related* to the study treatment.

## 7.3 Expedited Adverse Event Reporting

7.3.1 Expedited AE reporting for this study must use CTEP-AERS (CTEP Adverse Event Reporting System), accessed via the CTEP Web site (<http://ctep.cancer.gov>). The reporting procedures to be followed are presented in the “NCI Guidelines for Investigators: Adverse Event Reporting Requirements for DCTD (CTEP and CIP) and DCP INDs and IDEs” which can be downloaded from the CTEP Web site (<http://ctep.cancer.gov>). These requirements are briefly outlined in the tables below (Section 7.3.3).

In the rare occurrence when Internet connectivity is lost, a 24-hour notification is to be made to CTEP by telephone at [contact]. Once Internet connectivity is restored, the 24-hour notification phoned in must be entered electronically into CTEP-AERS by the original submitter at the site.

7.3.2 CTEP-AERS is programmed for automatic electronic distribution of reports to the following individuals: Study Coordinator of the Lead Organization, Principal Investigator, and the local treating physician. CTEP-AERS provides a copy feature for other e-mail recipients.

### 7.3.3 Expedited Reporting Guidelines

Use the NCI protocol number and the protocol-specific patient ID assigned during trial registration on all reports.

**Note: A death on study requires both routine and expedited reporting regardless of causality, unless as noted below. Attribution to treatment or other cause must be provided.**

Death due to progressive disease should be reported as **Grade 5 “Disease progression”** in the system organ class (SOC) “General disorders and administration site conditions. Evidence that the death was a manifestation of underlying disease (*e.g.*, radiological changes suggesting tumor growth or progression: clinical deterioration associated with a disease process) should be submitted.

**Table 21: Phase 1 and Early Phase 2 Studies: Expedited Reporting Requirements for Adverse Events that Occur on Studies under an IND/IDE within 30 Days of the Last Administration of the Investigational Agent/Intervention **

FDA REPORTING REQUIREMENTS FOR SERIOUS ADVERSE EVENTS (21 CFR Part 312)

NOTE: Investigators **MUST** immediately report to the sponsor (NCI) **ANY** Serious Adverse Events, whether or not they are considered related to the investigational agent(s)/intervention (21 CFR 312.64)

An adverse event is considered serious if it results in **ANY** of the following outcomes:

1) Death

2) A life-threatening adverse event

3) An adverse event that results in inpatient hospitalization or prolongation of existing hospitalization for ≥ 24 hours

4) A persistent or significant incapacity or substantial disruption of the ability to conduct normal life functions

5) A congenital anomaly/birth defect.

Important Medical Events (IME) that may not result in death, be life threatening, or require hospitalization may be considered serious when, based upon medical judgment, they may jeopardize the patient or subject and may require medical or surgical intervention to prevent one of the outcomes listed in this definition. (FDA, 21 CFR 312.32; ICH E2A and ICH E6).

**ALL SERIOUS** adverse events that meet the above criteria **MUST** be immediately reported to the NCI via CTEP-AERS within the timeframes detailed in the table below.

| Hospitalization                           | Grade 1 and Grade 2 Timeframes | Grade 3-5 Timeframes    |
|-------------------------------------------|--------------------------------|-------------------------|
| Resulting in Hospitalization ≥ 24 hrs     | 10 Calendar Days               | 24-Hour 5 Calendar Days |
| Not resulting in Hospitalization ≥ 24 hrs | Not required                   |                         |

NOTE: Protocol specific exceptions to expedited reporting of serious adverse events are found in the Specific Protocol Exceptions to Expedited Reporting (SPEER) portion of the CAEPR.

**Expedited AE reporting timelines are defined as:**

○ “24-Hour; 5 Calendar Days” - The AE must initially be reported via CTEP-AERS within 24 hours of learning of the AE, followed by a complete expedited report within 5 calendar days of the initial 24-hour report.

○ “10 Calendar Days” - A complete expedited report on the AE must be submitted within 10 calendar days of learning of the AE.

Serious adverse events that occur more than 30 days after the last administration of investigational agent/intervention and have an attribution of possible, probable, or definite require reporting as follows:  
**Expedited 24-hour notification followed by complete report within 5 calendar days for:**

- All Grade 3, 4, and Grade 5 AEs

**Expedited 10 calendar day reports for:**

- Grade 2 AEs resulting in hospitalization or prolongation of hospitalization

For studies using PET or SPECT IND agents, the AE reporting period is limited to 10 radioactive half-lives, rounded UP to the nearest whole day, after the agent/intervention was last administered. Footnote “1” above applies after this reporting period.

Effective Date: May 5, 2011

#### 7.4 Routine Adverse Event Reporting

All Adverse Events **must** be reported in routine study data submissions. **AEs reported through CTEP-AERS must also be reported in routine study data submissions.**

#### 7.5 Secondary Malignancy

A secondary malignancy is a cancer caused by treatment for a previous malignancy (*e.g.*, treatment with investigational agent/intervention, radiation or chemotherapy). A secondary malignancy is not considered a metastasis of the initial neoplasm.

CTEP requires all secondary malignancies that occur following treatment with an agent under an NCI IND/IDE be reported via CTEP-AERS. Three options are available to describe the event:

- Leukemia secondary to oncology chemotherapy (*e.g.*, acute myelocytic leukemia [AML])
- Myelodysplastic syndrome (MDS)
- Treatment-related secondary malignancy

Any malignancy possibly related to cancer treatment (including AML/MDS) should also be reported via the routine reporting mechanisms outlined in each protocol.

#### 7.6 Second Malignancy

A second malignancy is one unrelated to the treatment of a prior malignancy (and is **NOT** a metastasis from the initial malignancy). Second malignancies require **ONLY** routine reporting via CDUS unless otherwise specified.

### 8. PHARMACEUTICAL INFORMATION

A list of the adverse events and potential risks associated with the investigational agent administered in this study can be found in Section 7.1.

#### 8.1 Trametinib dimethyl sulfoxide (GSK1120212B, MEKINIST™) (NSC 763093)

**Chemical Name (IUPAC):**

equimolecular combination of acetamide, N-[3-[3-cyclopropyl-5-[(2-fluoro-4-iodophenyl)amino]-3,4,6,7-tetrahydro-6,8-dimethyl-2,4,7-trioxopyrido[4,3-d]pyrimidin-1(2H)-yl]phenyl] with 1,1'-sulfinylbis[methane]

**Other Names:** trametinib, GSK1120212, JTP-74057, JTP-78296, JTP-75303, Mekinist

**CAS Registry Number:** 1187431-43-1

**Classification:** MEK inhibitor

**Molecular Formula:** C26H23FIN5O4 • C2H6OS

**M.W.:** 693.53 (dimethyl sulfoxide solvate), 615.41 (anhydrous parent)

**Approximate Solubility:** Trametinib dimethyl sulfoxide is almost insoluble in water (<0.0001 mg/mL at 25° C)

**Mode of Action:** Trametinib dimethyl sulfoxide is a reversible, highly selective, allosteric inhibitor of mitogen-activated extracellular signal regulated kinase 1 (MEK1) and MEK2. Tumor cells commonly have hyperactivated extracellular signal-related kinase (ERK) pathways in which MEK is a critical component. Trametinib dimethyl sulfoxide inhibits activation of MEK by RAF kinases and MEK kinases.

**Description:** Trametinib dimethyl sulfoxide is a white to almost white powder.

**How Supplied:** Novartis supplies and CTEP, NCI, DCTD distributes 0.5 mg and 2 mg (as free base) tablets. Each investigationally-labeled bottle contains 32 tablets.

The tablet core contains mannitol, microcrystalline cellulose, hypromellose, croscarmellose sodium, magnesium stearate (non-animal), colloidal silicon dioxide and sodium lauryl sulfate.

- 0.5 mg tablets are yellow, modified oval, biconvex and film-coated. Aqueous film coating consists of hypromellose, titanium dioxide, polyethylene glycol, iron oxide yellow.
- 2 mg tablets are pink, round, biconvex and film-coated. Aqueous film coating consists of hypromellose, titanium dioxide, polyethylene glycol, polysorbate 80, iron oxide red.

**Storage:** Store tablets at 2°C - 8°C (36° F to 46° F) in the original bottle and dispense unopened bottles. Do not open bottles or repackaging tablets or remove desiccant. Bottles should be protected from light and moisture.

If a storage temperature excursion is identified, promptly return trametinib to 2°C -8°C and quarantine the supplies. Provide a detailed report of the excursion (including

documentation of temperature monitoring and duration of the excursion) to [[contact]](mailto:[contact]) for determination of suitability.

**Stability:** Stability studies are ongoing. Tablets are only stable for 32 days once bottle has been opened. If multiple bottles are dispensed to a patient in the same visit, please advise the patient to open only one bottle at a time.

**Route of Administration:** Oral. Take by mouth on an empty stomach, either 1 hour before or 2 hours after a meal. If a dose of trametinib is missed, the dose can be taken if it is more than 12 hours until the next scheduled dose.

### Potential Drug Interactions

*In vitro* studies suggest that trametinib dimethyl sulfoxide is not a substrate of CYP enzymes or of human BCRP, MRP2, OATP1B1, OATP1B3, OATP2B1, OCT1 or MATE1 transporters. Trametinib elimination by deacetylation to metabolite M5 is dependent on carboxylesterases (CES1b, CES1c and CES2). Trametinib is a substrate for P-gp and BSEP, but this is not expected to be clinically relevant due to trametinib's high permeability.

Trametinib dimethyl sulfoxide is an *in vitro* inhibitor of CYP 2C8, and is anticipated to have overall low potential for drug interactions as a perpetrator. It is also a weak CYP 2B6 and 3A4 inducer and expected to have little clinical effect on sensitive substrates. Trametinib is not an inhibitor of CYP 1A2, 2A6, 2B6, 2C9, 2C19, 2D6 and 3A4 and not an inhibitor of MRP2 or BSEP, but as *in vitro* inhibitor of P-gp, BCRP, OATP1B1, OATP1B3, OAT1, OAT3, OCT2 and MATE1 at systemic concentrations that are not clinically relevant. No clinically relevant inhibition by trametinib is predicted in the liver or kidney and a low risk of intestinal drug-drug interaction is possible with BCRP.

**Patient Care Implications:** Advise women study participants of reproductive potential to use effective contraception while receiving study treatment and for 4 months after the last dose of trametinib. Advise women not to breastfeed while receiving study treatment and for 4 months after the last dose of trametinib. Advise men study participants to use barrier contraception and not to father a child while taking study treatment and for 4 months after the last dose of trametinib.

### Availability

Trametinib dimethyl sulfoxide (GSK1120212B) is an investigational agent supplied to investigators by the Division of Cancer Treatment and Diagnosis (DCTD), NCI.

Trametinib dimethyl sulfoxide (GSK1120212B) is provided to the NCI under a Collaborative Agreement between the Pharmaceutical Collaborator and the DCTD, NCI (see Section 12.3).

### 8.1.1 Agent Ordering and Agent Accountability

8.1.1.1 NCI-supplied agents may be requested by the Principal Investigator (or their authorized designee) at each participating institution. Pharmaceutical Management Branch (PMB) policy requires that agent be shipped directly to the institution where the patient is to be treated. PMB does not permit the transfer of agents between institutions (unless prior approval from PMB is obtained). The CTEP-assigned protocol number must be used for ordering all CTEP-supplied investigational agents. The responsible investigator at each participating institution must be registered with CTEP, DCTD through an annual submission of FDA Form 1572 (Statement of Investigator), Curriculum Vitae, Supplemental Investigator Data Form (IDF), and Financial Disclosure Form (FDF). If there are several participating investigators at one institution, CTEP-supplied investigational agents for the study should be ordered under the name of one lead investigator at that institution.

Active CTEP-registered investigators and investigator-designated shipping designees and ordering designees can submit agent requests through the PMB Online Agent Order Processing (OAOP) application (<https://eapps-ctep.nci.nih.gov/OAOP/pages/login.jsp>). Access to OAOP requires the establishment of a CTEP Identity and Access Management (IAM) account (<https://eapps-ctep.nci.nih.gov/iam/>) and the maintenance of an “active” account status and a “current” password. For questions about drug orders, transfers, returns, or accountability, call [contact] Monday through Friday between 8:30 am and 4:30 pm (ET) or email [[contact]](mailto:[contact]) anytime.

8.1.1.2 Agent Inventory Records – The investigator, or a responsible party designated by the investigator, must maintain a careful record of the inventory and disposition of all agents received from DCTD using the NCI Drug Accountability Record Form (DARF). (See the NCI Investigator’s Handbook for Procedures for Drug Accountability and Storage.)

### 8.1.2 Investigator Brochure Availability

The current versions of the IBs for PMB-supplied agents will be accessible to site investigators and research staff through the PMB Online Agent Order Processing (OAOP) application. Access to OAOP requires the establishment of a CTEP Identity and Access Management (IAM) account and the maintenance of an “active” account status and a “current” password. Questions about IB access may be directed to the PMB IB coordinator at [[contact]](mailto:[contact]).

## 9. BIOMARKER, CORRELATIVE, AND SPECIAL STUDIES

### 9.1 Pharmacokinetic Studies

Pharmacokinetic studies will be performed on all enrolled patients to assess the bio-distribution of trametinib in patients with organ dysfunction. At the Principal Investigator’s discretion, this requirement may be waived in case of patient hardship, including lack of venous access. In this event, patients will be replaced to ensure that

adequate PK data are obtained for each group (i.e., at least 3 patients per group and at least 6 patients at the MTD level).

In blood, trametinib has been shown to be the predominant radio- component and M5 the only detectable minor component (<7% of the blood radioactivity). Plasma concentrations will be measured by Covance Laboratory Inc using a validated LC/MS/MS assay. All PK measurements for this study will be performed at Covance Laboratory Inc. All data and results will be made available to the investigators on this study and to CTEP. The minimum turnaround time for PK measurements will be 4 weeks from receipt of samples by the analytical laboratory. In patients who experience unexpected serious toxicity efforts will be made to have analysis available in 2 weeks. Availability of PK data is anticipated prior to dose escalation to another dose level.

PK sampling will be performed in cycle 1 for all patients. In patients with incomplete PK from cycle 1 and in those who change dose level or hepatic dysfunction group between cycles, repeat PK sampling is encouraged in subsequent cycles but is not mandatory. For severe liver dysfunction cohort, patients who complete PK schedule at day 16 will be considered evaluable for DLT assessment.

Specimen Collection and Analysis Details are provided in the “Pharmacokinetic Laboratory Manual” supplied by the Coordinating Central Office. Note: This will be disseminated with the clinical protocol and is also available to investigators on request from the coordinating center.

#### 9.1.1 Specimen Collection

The blood samples will be collected into 2 mL K2-EDTA vacutainers for all time points except Day 15 predose and 2 hours. At those two points, blood samples will be collected into 5 mL K2-EDTA vacutainers due to extra plasma protein binding measurement. Fill all blood tube completely and mix immediately by gently inverting the tube 8-10 times. Place collected blood on wet ice *immediately* after mixing with EDTA.

Pharmacokinetic study will start on C1D15 of the trial. The times of drug administration on Day 15 and 16 should be recorded on the specimen collection form.

#### 9.1.2 Specimen Collection Schedule

Plasma will be collected on Day 15 of Cycle 1 according to the following schedule: before drug administration and at the following times after administering the oral dose: 0.5, 1, 2, 3, 4, 6, 10 and 24 hours (+/- 10 minute window). Thus, 9 samples will be collected in Cycle 1.

To evaluate trametinib plasma protein binding measurements, additional blood samples will be collected on Day 15 before trametinib dose and 2 hours after trametinib dose (+/- 10 minute window).

Sampling Schedule is summarized in following Table (Table 22).

**Table 22:** Pharmacokinetic sample collection schedule.

| Sample Number | Day of Collection | Planned Collection Time (hours) |
|---------------|-------------------|---------------------------------|
| 1*            | 15                | 0 (Pretreatment)                |
| 2             | 15                | 0.5                             |
| 3             | 15                | 1.0                             |
| 4*            | 15                | 2.0                             |
| 5             | 15                | 3.0                             |
| 6             | 15                | 4.0                             |
| 7             | 15                | 6.0                             |
| 8             | 15                | 10                              |
| 9             | 16                | 24                              |

\* 5mL of blood should be collected to generate 1.5 mL of plasma samples for pharmacokinetics and plasma protein binding analysis.

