#### 2.2.1.2 Clinical Pharmacokinetics (PK) and Activity of Trametinib

##### FTIH Phase 1 Trial of Trametinib Monotherapy (MEK111054)

There are 3 parts in this study. Part 1: The dose-escalation portion involves administration of trametinib (repeat doses of 0.125 mg to 4.0 mg) to patients with solid tumors or lymphoma in one of three schedules - (1) QD for 21 days followed by 7 days without drug, (2) loading dose on Day 1 or Day 1-2, followed by QD with the

designated dose, or (3) QD dosing without a drug holiday. Part 2: cohort expansion at the recommended phase 2 dose (RP2D) for pancreatic cancer, melanoma, non-small cell lung cancer (NSCLC), colorectal cancer (CRC), or any BRAF mutation-positive cancer. Part 3: expansion to characterize the biologically active range of trametinib via analysis of pharmacodynamic biomarkers (biopsies or FDG-PET).

The MTD of trametinib was established as 3 mg QD, but the recommended phase 2 dose (RP2D) was chosen at 2 mg QD based on tolerability of repeated cycles.

*PK and metabolism of trametinib:*

PK measurements were conducted under fasting conditions. After a single dose (Day 1), AUC0-24 and Cmax values were dose-proportional up to 6 mg, lower than dose proportional following 8 mg, and greater than dose proportional following the 10 mg dose. Median Tmax was 1.5 hours.

After repeat doses (Day 15), trametinib accumulated with a mean accumulation ratio of 6.6 at the RP2D of 2 mg QD. Between-subject variability in exposure ranged from 27-50% for Cmax and 20-41% for AUC0-24 across all dosing regimens. The effective t1/2 was approximately 4.5 days, and steady state was reached by approximately Day 15. Trametinib had a small peak: trough ratio of ~2. At 2 mg QD on Day 15, mean AUC0-24 was 376 ng•h/mL and Cmax 23 ng/mL, and the mean trough concentrations ranged from 10.0 to 18.9 ng/mL. The long half-life and small peak: trough ratio of trametinib allowed constant target inhibition within a narrow range of exposure.

*Drug-drug interactions:*

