## 2.4 Rationale

The effect of trametinib in subjects with a variety of refractory cancers has been evaluated in several clinical trials, administered as both single agent or in combination. Trametinib pharmacokinetics was determined after single and repeat-dose oral administration of study medication tablets in subjects with solid tumors. Results showed that trametinib is absorbed rapidly with median Tmax generally occurring 1.5 hours after single oral administration under fasting conditions. The absolute oral bioavailability of a single trametinib 2 mg tablet is moderate to high (72%) relative to a co-administered IV microdose. Single-dose administration of trametinib with a high-fat, high-calorie meal resulted in a 70% decrease in maximum observed concentration (Cmax) and a 10% decrease in area under the concentration-time curve from time zero (pre-dose) extrapolated to infinity (AUC(0-∞)) compared to fasted conditions. Following repeat-dosing the mean area under the curve (AUC0-τ) and maximum concentrations (Cmax) increased in an approximately dose proportional manner. Trametinib dose accumulation has been seen with repeat dosing with a mean accumulation ratio at the RP2D of 2 mg once daily of 5.97 and a terminal half-life of 5.3 days, determined after single dose administration. Steady state appears to be achieved by Day 15, with little difference in pre-dose (trough) concentration at the end of the dosing interval (Cτ), Cmax and area under the concentration-time curve from time zero (pre-dose) to 24 hours (AUC(0-24)) between Days 15 and 21. Additionally, trametinib is a low extraction ratio drug based on plasma IV clearance of 3.21 L/hour, which represents approximately 1% of liver blood flow. Trametinib has a high

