volume of distribution (Vd) of 1060 L determined following an IV microdose. Furthermore, data from previous studies have shown that fecal excretion is the major route of elimination following trametinib oral dose. This route accounts for >80% of excreted radioactivity recovered (or 39.2 and 35.0% of the radioactive dose in 2 subjects) while urinary excretion accounts for <19% of excreted radioactivity recovered (<10% of the radioactive dose). Given that trametinib is generally deacetylated via hydrolytic esterases, therefore its pharmacokinetics is unlikely to be affected by other agents through metabolic interactions. Based on *in vitro* and *in vivo* data trametinib is unlikely to significantly affect the pharmacokinetics of other products via interactions with CYP enzymes or transporters, and that the PK of trametinib is unlikely to be affected by other drugs.

In the population PK analysis of trametinib, 64 (13.0%) subjects were categorized as having mild hepatic impairment (NCI classification). Exposure to trametinib was not significantly different in these subjects (2% difference) relative to subjects with normal hepatic function.

Currently, no clinical data on trametinib are available in patients with hepatic dysfunction. Data have shown that hepatic metabolism is likely to be the primary route of elimination and it can be anticipated that trametinib concentrations will increase in patients with hepatic impairment; hence dose adjustment may be needed. Taken together all these pharmacokinetic considerations and given that trametinib has not been evaluated in patients with hepatic dysfunction; it is of interest to investigate safety and pharmacokinetic assessments of trametinib in this patient population prior to routine use and dosing recommendations.

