### 9.1.5 Pharmacokinetic Analysis

The following trametinib PK parameters will be calculated based on results collected for each Cohort:

- Maximum plasma concentration (Cmax)
- Time to maximum concentration (Tmax)
- Steady state concentration (Css)
- Trough concentrations at steady-state (Css,min)
- Terminal half-life (t1/2) clearance
- Area under the plasma concentration-time curve for 0-24 h or tau (AUC0-24h/tau)

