† If baseline labs are within 1 week of the start of protocol therapy, labs do not need to be repeated on cycle 1 day 1. Only the liver function tests (AST and total bilirubin) to confirm the cohort assignment need to be repeated within 24 hours of cycle 1 day 1.

1. All screening assessments must be completed within 1 week prior to first dose except archival tumor tissue and imaging analyses
2. Safety assessments will continue every 2 weeks while the subject remains on study medication(s), with the exception of urinalysis which will be every 4 weeks, ECHO/MUGA will be performed every 12 weeks unless clinically indicated. Efficacy assessments will occur every 2 cycles (approximately 8 weeks), unless required to confirm a response or as clinically indicated.
3. Discontinuation visit should be 14 days from last dose of study medication(s).
4. Dermatologic exams should be performed by the Investigator, or may be referred to a dermatologist, at the discretion of the investigator for patients. Dermatologic exam should be performed at baseline and then repeated as clinically indicated.
5. Height and weight at screening only; weight only at other indicated visits.
6. Hematology/Clinical Chemistry includes CBC with differential, sodium, chloride, potassium, bicarbonate, creatinine, AST, ALT, ALP, bilirubin, albumin, calcium, magnesium, and phosphate. Note: liver function tests must be performed 24 hours prior C1D1.
7. Serum pregnancy test should be performed within 14 days of administration of the first dose of study medication; all subsequent pregnancy tests may be either serum or urine.
8. Ophthalmology Exam: Fundoscopy, tonometry, visual field examination, slit lamp biomicroscopic examination, and corrected visual acuity assessments at baseline screening and when clinically indicated during study. Note: Optical coherence tomography is recommended if retinal abnormalities are suspected
9. Disease Characteristics: Record date of diagnosis, primary tumor type, histology, stage, etc.
10. Applicable tumor markers include CA125 (ovary), CA19-9 (ampullary, biliary), and CEA (small bowel).
11. Pharmacokinetic sampling: C1D15 (up to 10 hours), C1D16 (24 hours) (+/- 10 minute window).
12. One tube of whole blood will be obtained at C1D1 (or anytime during study) in all patients to provide a source of germline DNA.

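### One 24-hour profile on Day 15 cannot give the terminal half-life listed in Section 9.1.5, and reading it as steady state would shrink any exposure increase in Groups C and D that comes from slower clearance

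*Protocol*

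**What the plan says.** Section 1.1 makes characterising the PK profile by degree of hepatic dysfunction a primary objective. The text after Table 10 names the normal cohort as the PK comparison.

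Section 9.1.2 takes a pre-dose sample on Day 15 and then samples at "0.5, 1, 2, 3, 4, 6, 10 and 24 hours (+/- 10 minute window). Thus, 9 samples will be collected in Cycle 1". The calendar notes in Section 10 confirm this: "Pharmacokinetic sampling: C1D15 (up to 10 hours), C1D16 (24 hours) (+/- 10 minute window". Section 9.1.1 starts PK on C1D15 and asks for dosing times on both Day 15 and Day 16, so there is neither a first-dose profile nor a washout. Under Section 9.1, later sampling is encouraged but optional, and only for patients with incomplete Cycle 1 PK or a change of dose level or group.

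Section 9.1.5 lists the parameters for each cohort. They include "Terminal half-life (t 1/2 ) clearance" (two items apparently run together), a steady-state concentration, "Trough concentrations at steady-state" and an AUC over 0 to 24 h or tau.

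On the drug itself, Section 2.2.1.2 says the effective half-life "was approximately 4.5 days, and steady state was reached by approximately Day 15". Section 2.4 gives "a terminal half-life of 5.3 days, determined after single dose administration". Section 2.4 also states that clinical data in hepatic dysfunction are lacking and that "it can be anticipated that trametinib concentrations will increase in patients with hepatic impairment".

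**The concern.** Two listed outputs do not match the sampling.

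First, a terminal half-life needs concentrations followed over a useful part of the elimination phase. One dosing interval of a drug with a half-life near five days does not provide that. Without a Day 1 profile, a half-life cannot be derived from accumulation either.

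Second, time to steady state depends on half-life. The Day 15 figure was learned in general trial populations. If elimination is slower in moderate or severe impairment, those patients are further below their own plateau on Day 15 than Group A is below its plateau. Calling both sets of values steady state would then make the exposure difference look smaller than it is. At stake is the size of the PK effect reported under a primary objective. Samples that were never drawn cannot be recovered at analysis.

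**Working it through.** **Inputs from the protocol.** Half-life 4.5 d (2.2.1.2) and 5.3 d (2.4); accumulation ratios 6.6 (2.2.1.2) and 5.97 (2.4); peak-to-trough ratio about 2 and median Tmax 1.5 h (2.2.1.2); one 24 h profile at the 15th daily dose.

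**Assumed, because the protocol gives no figure.** True AUC ratios of 1.25 to 3; one-compartment kinetics; lower clearance at unchanged volume, so that half-life rises in proportion; concentration error of 5 to 15% for the slope.

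**Step 1: reproduce the plan's figures.** After n daily doses, the fraction of steady state reached is f(n, t) = 1 − 2^(−n/t), with half-life t in days.
- At t = 4.5, accumulation at the 15th dose is f(15)/f(1) = 0.901/0.1428 = 6.31, and at plateau 1/0.1428 = 7.00. These bracket the stated 6.6.
- Day 15 is at 90% of steady state (t = 4.5) or 86% (t = 5.3). Day 21 would exceed Day 15 by only 7 to 9%.
- So steady state by about Day 15 is a fair description for normal clearance.

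**Step 2: terminal half-life.**
- Window: 1/4.5 = 0.22 and 1/5.3 = 0.19 of a half-life.
- Decline over 24 h: 1 − 2^(−1/4.5) = 14%; 1 − 2^(−1/5.3) = 12%.
- True slope: ln 2/(4.5 × 24) = 0.0064 per hour; ln 2/(5.3 × 24) = 0.0055 per hour.
- Log-linear fit through 6, 10 and 24 h: mean time 13.33 h, sum of squares 53.8 + 11.1 + 113.8 = 178.7. At 10% error, SE = 0.10/√178.7 = 0.0075 per hour, larger than the slope.
- In simulation, the fitted slope is zero or positive in 4%, 19% and 28% of patients at 5%, 10% and 15% error when t = 4.5 d. When t = 9 d (clearance halved), it is zero or positive in 20%, 33% and 39%.
- A fall by a factor of about 2 from 1.5 h to 24 h would read as a half-life near 22.5 h, not 4.5 to 5.3 days. Distribution dominates the interval.

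**Step 3: Day 15 ratio against Group A.** For a true ratio m, the observed ratio is m × f(15, m·t)/f(15, t). For m = 2: 2 × 0.685/0.901 = 1.52 (t = 4.5) and 2 × 0.625/0.859 = 1.45 (t = 5.3).

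| True AUC ratio | Seen, t = 4.5 d | Seen, t = 5.3 d |
|---|---|---|
| 1.25 | 1.17 | 1.15 |
| 1.5 | 1.31 | 1.27 |
| 2 | 1.52 | 1.45 |
| 3 | 1.79 | 1.68 |

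With the shorter half-life implied by the ratio of 5.97 (about 3.8 d by the plateau formula), 1.25 reads 1.19 and 2 reads 1.59. The direction is the same and the loss somewhat smaller.

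**Step 4: what later troughs would add.** With clearance halved (half-life 9 to 10.6 d), the Day 15 pre-dose sample follows 14 doses and is at 60 to 66% of steady state. C2D1 pre-dose follows 28 doses: f = 0.84 to 0.88. C3D1 follows 56: f = 0.97 to 0.99. These figures assume uninterrupted dosing.

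**The case against.** The best reply is that little turns on these values. The recommended dose follows DLT counts (Table 10 and Section 13.3) and the ordering constraint between groups in Section 13.1. PK results are only expected to be available before escalation, and no rule acts on them. The PK objective is descriptive, with no test or margin. This stands. A reader might infer that the attenuation pushes the recommended doses in an unsafe direction; the documents do not support that.

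Slower clearance is also an expectation, not a result. Section 2.4 reports a 2% exposure difference in 64 subjects with mild impairment, so Group B is probably little affected. A rise through bioavailability alone would not be attenuated in this way. AUC over 0 to 24 h is a valid Day 15 quantity as labelled. All of this stands, and it limits the point to half-life, Css and Css,min, and to Groups C and D.

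Three further inferences should be resisted.
- Dividing the quoted volume by the quoted IV clearance gives ln 2 × 1060/3.21 = 229 h, or 9.5 d, which suggests that even Group A is far from plateau. That conflicts with both stated half-lives. It would put Day 21 about 18% above Day 15, which sits badly with the near-equality reported in Section 2.4.
- Bioavailability and IV clearance imply an AUC of 2 mg × 0.72/3.21 L/h = 449 ng·h/mL, against the reported 376. This is a cross-study comparison, and a 16% gap beside 20 to 41% between-subject variability shows nothing firm.
- Protein binding is sampled ("collected into 5 mL K2-EDTA vacutainers due to extra plasma protein binding measurement") and no unbound parameter is listed. Deriving one is ordinary analysis detail that can be set elsewhere, so it is not a fault here.

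Day 15 also suits Group D, where Section 13.1 expects quick deterioration. That is a reason to keep the profile, but not to call it steady state.

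**Conclusion.** The half-life point holds without reservation: Section 9.1.5 names a parameter that the mandatory sampling cannot deliver, and the estimate gets worse as clearance slows. The steady-state point holds in direction if clearance falls in Groups C and D. Its size is conditional on one-compartment kinetics, unchanged volume and a true ratio that no document supplies: 1.25 reads about 1.15 to 1.17, and 2 reads about 1.45 to 1.52. A 2-fold rise loses about half of its excess but stays visible, so this is attenuation, not abolition. The effect falls on the primary PK characterisation, not on the DLT-based dose rule. It should be fixed, but it does not undermine the dose-finding.

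**What to change.** - Delete terminal half-life from Section 9.1.5, and separate it from the clearance entry. A single tube at the end-of-treatment visit would not rescue it, because one concentration gives no slope.
- Report Css and Css,min as Day 15 average and trough concentrations. Keep AUC over 0 to 24 h as a Day 15 value. Do not describe any of these as steady state in Groups C and D.
- For patients still on treatment, add one pre-dose 2 mL PK tube to the blood draws already scheduled at C2D1 and C3D1 (Table 24). Estimate CL/F with a model that uses the actual dosing record, for which the medication diary already collects dose times, instead of assuming steady state.

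The first two changes cost only wording. The third needs an amendment and two extra tubes and assays per patient. Its limits should be stated in the report: later troughs come only from patients who remain on treatment, which may be few in Group D, and only from those enrolled after the amendment. By the C2D1 sample the attenuation is reduced but not removed.
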